### Sample size estimation

The main objective of our study is to assess the non-inferiority of the risk of complications while maintaining OAC treatment in patients with BPO who are undergoing surgery via GreenLight PVP. The risks of complication are assessed using the following binary criteria:Complication = 1 if at least one complication is classified as ≥2 according to the Clavien-Dindo classificationComplication = 0 if the only complications that occur are classified as < 2 according to the Clavien-Dindo classification.

Our literature analysis failed to find published references on the risks of complications for any of the two management strategies assessed in the current study. However, the analysis of a single-centre PVP database of the Clinique Pasteur (Toulouse, France) makes it possible to estimate the proportion of patients presenting with “complication = 1”. This estimated risk is 13.2% (95% confidence interval [0.091, 0.183]). The assumption of our study is that this proportion of 13.2%, which was obtained on the basis of patients of the Clinic Pasteur, will be obtained for each of the two strategies under study. The margin of non-inferiority will be set at 10%, which is clinically reasonable. The value of the non-inferiority margin was defined after a non-informal survey of clinical experts who have experimented with both intervention strategies.

Using two-tailed 95% confidence intervals, non-inferiority would be identified with 80% power up to a non-inferiority margin of 10% if approximately 350 participants are randomized to the study. Thirty-nine patients will be added to account for potential withdrawals during the trial.

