**Methods:**

This study is a multicentre, open-label, randomized controlled trial (RCT) designed to show the non-inferiority of PVP surgery in patients with BPO treated with OACs. This study is designed to enrol 386 OAC-treated patients (treated with vitamin K antagonists and direct oral anticoagulants) who are undergoing PVP for BPO. Patients will be randomized (1:1) to either maintain or stop OAC treatment during the perioperative course. The intervention group will maintain OAC treatment until the day before surgery and resume OAC treatment the day after surgery, whereas the control group will stop OAC treatment (with or without low-molecular-weight heparin bridging therapy) according to the anaesthesia guidelines. The primary outcome of interest to be assessed is the 30-day complications rate according to the Clavien-Dindo classification. The secondary endpoint will examine the 30-day rate of haemorrhagic and thrombotic events. This study will provide 80% power to show non-inferiority, defined as not worse than a 10% (non-inferiority margin) inferior change in the proportion of patients with good outcomes (Clavien-Dindo score < 2), using two-tailed 95% confidence intervals.

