### Trial status and timeline

As of 30 September 2018, 30 patients were enrolled, and recruitment is ongoing. Approximately 11 institutions are preparing to begin patient enrolment. A total of 386 patients will be recruited for the trial within 2 years.

The recruitment of patients started in January 2018 and will finish in January 2020.

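### The 80% power is slightly overstated for about 350 patients, and the printed base, withdrawal allowance and total (350, 39, 386) agree only through an unprinted base of 347

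*Protocol article*

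**What the plan says.** All references are to the protocol article.

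- **Sample size estimation, power.** The section sets "Using two-tailed 95% confidence intervals" and says that "non-inferiority would be identified with 80% power" at a 10% margin "if approximately 350 participants are randomized to the study".
- **Sample size estimation, event rate.** A complication risk of 13.2% from a single-centre database (95% CI 9.1% to 18.3%) is assumed and "will be obtained for each of the two strategies under study".
- **Sample size estimation, withdrawals.** "Thirty-nine patients will be added to account for potential withdrawals during the trial". No withdrawal percentage is given.
- **Abstract, Methods.** "This study is designed to enrol 386 OAC-treated patients".
- **Trial status and timeline.** "A total of 386 patients will be recruited for the trial within 2 years".
- **Statistical methods.** The primary endpoint is analysed in a per-protocol set and in a modified intention-to-treat set limited to patients who had surgery.

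**The concern.** Two things catch the eye.

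First, a reader who adds the base and the allowance gets 389, not the 386 given in the abstract and the timeline. The number of patients expected to remain after withdrawals is then unclear: it could be 350 or 347.

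Second, the inputs are complete enough to recompute the sample size, and the standard formula asks for somewhat more than 350.

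The section also attaches the 80% to patients randomised and then adds more for withdrawals, so it does not say which count carries the power. That matters because both primary analysis sets can leave out randomised patients. At stake are the recruitment target and the power claim. The margin, the analysis and the decision rule are not affected.

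**Working it through.** **Inputs** (Sample size estimation, with 1:1 allocation from Randomization)

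- Complication rate p = 0.132 in each arm, so the true difference is 0
- Non-inferiority margin 0.10, absolute
- Two-sided 95% interval, so z = 1.960 on the side that matters
- Power 80%, so z = 0.842

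**Step 1. The plan's own figure.** With the unpooled normal approximation,

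n per arm = (1.960 + 0.842)² × 2 × p(1 − p) / margin²
= 7.849 × 2 × 0.132 × 0.868 / 0.01 = 179.9 (7.849 is the square before the z values are rounded).

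That is 180 per arm, or 360 evaluable in total. The printed figure of approximately 350 is 10 lower, which is under 3%. It is close but slightly low.

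**Step 2. Could another convention give 350?** None of those tried does:

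| Convention | Total N |
|---|---|
| One-sided 0.05, 80% power | 284 |
| Unpooled, one-sided 0.025, 80% power | 360 |
| Farrington-Manning, one-sided 0.025, 80% power | about 377 |
| Two one-sided tests for equivalence at 0.05, 80% power | about 392 |
| Continuity-corrected, one-sided 0.025, 80% power | about 399 |
| Unpooled, one-sided 0.025, 90% power | 482 |

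The only one that needs fewer than 350 abandons the stated two-sided 95% interval.

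**Step 3. The three printed counts.**

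- As printed: 350 + 39 = 389, and 350/0.90 = 388.9. On this reading the allowance is 39/389 = 10.0%, and the total should be 389.
- Working back from 386: 386 − 39 = 347, and 347/0.90 = 385.6, rounded up to 386. On this reading the allowance is again about 10%, and 350 is a rounded 347.
- If 350 and 386 are both exact: 386 − 350 = 36, a loss of 36/386 = 9.3%, and the 39 does not fit.

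Only the second reading satisfies all three figures, and it needs a base that is not printed.

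**Step 4. Power at each count.** Normal approximation:

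power = Φ(0.10 / √(4 × 0.132 × 0.868 / N) − 1.960)

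| Evaluable N | Standard error | Power |
|---|---|---|
| 347 | 0.0363 | 78.6% |
| 350 | 0.0362 | 78.9% |
| 360 | 0.0357 | 80.0% |
| 386 (no losses) | 0.0345 | 82.7% |

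**Step 5. Does the interval method rescue 80%?** Exact enumeration of the binomial outcomes gives these powers for the two intervals; the Farrington-Manning column is from its normal-theory formula:

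| Evaluable N | Wald, exact | Newcombe, exact | Farrington-Manning |
|---|---|---|---|
| 347 | 78.4% | 77.7% | 76.6% |
| 350 | 79.4% | 78.4% | 76.9% |

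None reaches 80% at 347 or 350.

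**The case against.** The strongest reply is that the base is explicitly approximate. If it is 347, then dividing by 0.90 gives both the allowance of 39 and the total of 386, with the correct inflation formula and no error in the sum. This stands. It means the printed figures cannot be called an arithmetic mistake, only figures that a reader cannot reconcile without guessing the base.

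A reader might also infer that the total came from multiplying the base by 1.10 instead of dividing by 0.90. The document does not support this. No loss rate is stated, 350 × 1.10 is 385 and not 386, and multiplying by 1.10 would add 35 patients and not 39.

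The next reply is that a point of power is trivial beside the uncertainty in the event rate. This is largely right. A rate of 12.8% would give 4 × 0.128 × 0.872 × 7.849 / 0.01 = 350 in total, and over the 9.1% to 18.3% interval the same formula runs from about 260 to about 470. But the plan fixes 13.2% and quotes 80% for it, and on that assumption the quoted power is a little high.

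Finally, a journal article condenses the full protocol, where the exact base and loss rate may be given. Their absence alone would not be a fault. What remains is that figures the article does print give 389 in one place and 386 in two others, and that the printed power is slightly above what the printed inputs deliver.

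**Conclusion.** The point holds as a minor reporting correction. On the plan's own inputs, 80% power needs about 360 evaluable patients under the unpooled normal approximation. The evaluable number implied by the plan is 350 or 347, with power of 78.9% or 78.6%, so the claim is 1.1 to 1.4 points too high. Under the other methods tried the shortfall runs from 0.6 points (exact Wald at 350) to 3.4 points (Farrington-Manning at 347).

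A reader might conclude that the trial is materially underpowered. The figures do not support that. The base is within 3% of the computed requirement, and with no losses 386 patients would give 82.7%.

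The result assumes a rate of 13.2% in both arms and no true difference. The 10% loss is inferred from the 39 and is not stated; if only 36 of the 386 were lost, 350 would remain.

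**What to change.** In the abstract, Sample size estimation and Trial status and timeline, give one randomised total. In Sample size estimation, add the exact evaluable base and the assumed withdrawal rate, show the total as base/(1 − rate), and attach the power to the evaluable number and not to the number randomised. Either of these is consistent at a 10% loss:

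- keep 386 randomised, with 347 evaluable and power of 78.6%; or
- state 389 randomised, with 350 evaluable and power of 78.9%.

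In both cases the text would say about 79% and name the approximation used. The cost is a few words and a power figure about one point less favourable. Keeping 386 requires no extra enrolment. Holding the full 80% after a 10% loss would take 360/0.90 = 400 randomised, but a gap this small does not call for it.

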### Statistical methods

All statistical analyses will be thoroughly performed by independent statisticians who are not involved in patient treatment or outcome assessment. The statisticians will be blinded to the allocation code. The statisticians will perform statistical analyses according to predetermined data handling and statistical methods, and there will be no arbitrary interference. All analyses will be performed on per-protocol (PP) and intention-to-treat (ITT) populations in accordance with the recommendations on non-inferiority trials [19].

Baseline characteristics by group will be compared using descriptive analyses.

For the primary endpoint, the judgement criterion analysis will be performed using the non-inferiority confidence intervals approach. These analyses will be carried out on the per-protocol population (patients with no major deviation from the protocol that may affect the assessment of the primary endpoint) and the ITT model (ITT-m) population (ITT and underwent surgery).

Assessments of the quantitative criteria will be carried out by means of *t* tests if the distribution permits or by non-parametric methods (Wilcoxon-Mann-Whitney test). Assessments of the qualitative criteria will be made by means of proportional comparisons via chi-square tests. Subgroup assessments will be considered based on stratification factors of randomization (i.e. the centres and the presence of indwelling catheter at baseline).

To evaluate non-inferiority, the hypothesis testing strategy will follow the two one-sided tests (TOST) procedure developed by Schuirmann [20]. To assess superiority, the hypothesis testing strategy will be two-tailed. A *P* value of 0.05 will be considered statistically significant. All data analyses will be performed using SAS® (version 9.4 or later) or R.

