## Methods/design

### Study design

Stopping or maintaining oral anticoagulation in patients undergoing PVP (SOAP) is a randomized, open-label, multicentre, non-inferiority trial with two parallel groups. Patients will be allocated 1:1 to either the intervention group (S1) or the control group (S2). This study will be conducted in 11 centres in France. This study seeks to assess whether maintenance of OAC treatment increases the risk of adverse events (AEs) in patients undergoing PVP. Postoperative complications will be identified according to the Clavien-Dindo classification [13, 14]. This trial is registered with ClinicalTrials.gov (NCT03297281).

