### Outcome measures

The primary outcome is the number of patients with at least one complication classified greater than or equal to grade 2 according to the Clavien-Dindo classification at the 30 days follow-up. An independent adjudication committee composed of two surgical urologists will meet every 6 months to review the AEs and to validate the judgement criteria. This committee will be blinded to the randomization.

Secondary outcomes are the number of patients with at least one complication classified as greater than or equal to grade 2 according to the Clavien-Dindo classification at 6 months and the number of patients with at least one haemorrhagic or thrombotic complication at 1 month and 6 months. Moreover, the duration of catheterization, the length of hospital stay, the prostatic residual volume, PSA level, IPSS score, IPSS question 8 and USP, uroflowmetry (Qmax) and post-voiding residual will be collect during the follow-up visits.

Bleeding complications are defined as follows: a significant and persistent haematuria in a patient with or without a urethral catheter (Clavien 2) leading to a decrease in haemoglobin of 2 g/dl or more; a gross haematuria requiring clot removal through the bladder catheter under local anaesthesia (Clavien 3a) or with a cystoscope under general anaesthesia (Clavien 3b); and bleeding appearing in the immediate postoperative course, with the requirement of a red blood cell transfusion (Clavien 2).

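### The binary secondary safety outcomes are assigned a chi-square test of zero difference, which puts no limit on excess risk; a risk difference with a confidence interval would fit the trial's question better

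*Protocol article*

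**What the plan says.** The Study design section of the protocol article frames the question in one direction: "This study seeks to assess whether maintenance of OAC treatment increases the risk of adverse events (AEs) in patients undergoing PVP".

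The Outcome measures section lists these binary secondary outcomes:
- the count for "patients with at least one complication classified as greater than or equal to grade 2 according to the Clavien-Dindo classification at 6 months", which is the primary criterion at a later time;
- "the number of patients with at least one haemorrhagic or thrombotic complication at 1 month and 6 months".

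The Statistical methods section then gives three statements about testing:
- "For the primary endpoint, the judgement criterion analysis will be performed using the non-inferiority confidence intervals approach";
- "Assessments of the qualitative criteria will be made by means of proportional comparisons via chi-square tests", where a P "value of 0.05 will be considered statistically significant";
- a closing statement that non-inferiority is evaluated by the two one-sided tests "procedure developed by Schuirmann [20]. To assess superiority, the hypothesis testing strategy will be two-tailed". It does not say which outcomes it covers.

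The only margin, 10 points, is in the Sample size estimation section. It is set for the grade 2 or higher criterion, which Outcome measures makes the 30-day primary. No rate, margin or interval is given for the binary secondary outcomes.

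**The concern.** The method named for the binary safety outcomes fits the question poorly. A chi-square test asks whether the data are compatible with no difference. It can reveal an increase in risk, but when it does not, it says nothing about how large an increase remains possible. The reader of this trial wants exactly that bound: how much extra bleeding, or how many extra complications by 6 months, can be ruled out when anticoagulation is maintained.

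This bears on outcomes that matter. The abstract names bleeding and thrombotic events as the secondary endpoint, and Outcome measures says the Clavien-Dindo scale is too imprecise for thrombotic events. The primary analysis therefore cannot fully stand in for them. If a non-significant P is the headline result, the only outcome of the stated test that could seem favourable is one that excludes no particular excess.

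**Working it through.** **Inputs.** From Sample size estimation: expected rate 13.2% in both arms, margin 10 points, two-sided 95% interval, 80% power, about 350 patients (175 per arm). From Trial status and timeline: 386 recruited (193 per arm). The 13.2% is the planning rate for the primary criterion. The document gives no 6-month, bleeding or thrombotic rate, so every other control rate below is an assumption, shown as a range.

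**1. The plan's own figure.** For non-inferiority with equal rates, n per arm = (1.96 + 0.842)² × 2p(1 − p) / margin².
- 7.849 × 2 × 0.132 × 0.868 / 0.10² = 179.9, so 180 per arm or 360 in total, against about 350 stated (2.9% apart).
- At 175 per arm, SE = √(2 × 0.132 × 0.868 / 175) = 0.0362. Power = Φ(0.10/0.0362 − 1.96) = 78.9%, close to the stated 80%.

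The primary calculation is reproduced.

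**2. How often the chi-square is non-significant under true harm.** Z = (p2 − p1) / √(2p̄(1 − p̄)/n), with p1 and p2 the observed proportions and p̄ the pooled proportion. The result is non-significant if |Z| < 1.96. The probability is the exact sum over both binomial distributions, without continuity correction.

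| Control rate | True excess in S1 | Non-significant, 175 per arm | Non-significant, 193 per arm |
|---|---|---|---|
| 13.2% (protocol) | 3 points | 87% | 87% |
| 13.2% | 5 points | 75% | 73% |
| 13.2% | 7.5 points | 53% | 49% |
| 13.2% | 10 points | 31% | 27% |
| 20% (assumed, 6 months) | 5 points | 80% | 78% |
| 20% | 10 points | 42% | 38% |
| 5% (assumed, bleeding) | 5 points | 57% | 53% |
| 5% | 10 points | 11% | 8% |
| 1% (assumed, thrombosis) | 1 point | 90% | 89% |
| 1% | 2 points | 75% | 73% |

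Hand check at 13.2% against 23.2%, 175 per arm: p̄ = 0.182, null SE = 0.0412, alternative SE = 0.0409. Power ≈ Φ((0.10 − 1.96 × 0.0412)/0.0409) = Φ(0.47) = 68%, against 68.8% exact.

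**3. Sparse counts.** With 1% against 3% and 175 per arm, expected events are 1.75 + 5.25 = 7. Under the null that is 3.5 per arm, below the usual minimum of 5 for a chi-square.

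**4. What the interval adds.** Take 23/175 (13.1%) in control and 36/175 (20.6%) in S1.
- Difference = 13/175 = 7.4 points; p̄ = 59/350 = 0.169; Z = 0.0743/0.0400 = 1.86; P = 0.063.
- Unpooled SE = √(0.131 × 0.869/175 + 0.206 × 0.794/175) = 0.0398. The 95% interval is 7.4 ± 7.8 points, or −0.4 to +15.2.

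The P value says only that zero is not excluded. The interval shows that an excess of up to about 15 points is not excluded either.

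**The case against.** The strongest reply is that a misuse is being imputed. A reader might infer that the trial will declare maintained anticoagulation safe on a non-significant P. The document does not say so, and it states no non-inferiority hypothesis for any secondary outcome. That stands.

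Four further points have weight.
- A two-sided test is legitimate where effects may go either way. The Discussion says that interrupting treatment exposes patients to thromboembolism and haemorrhage, so these outcomes could favour S1. True, and an interval serves both directions at least as well.
- The statement on two one-sided tests names no outcome, so it is an inference that the chi-square is the only method. It remains the natural reading, because that procedure needs a margin and the sole margin belongs to the primary criterion.
- This is a condensed article, and intervals for secondary outcomes are commonly left to the analysis plan. The absence of an interval would not by itself be a finding. The point is that a method is stated and it suits the question poorly.
- Limited power for secondary outcomes is ordinary, and an interval does not cure it. Agreed: it shows the uncertainty rather than hiding it.

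A reader might also see a contradiction in the worked example, since the same counts give P = 0.063 and yet fail a 10-point margin. There is none. Not rejecting equality and not showing non-inferiority are compatible answers to different hypotheses.

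**Conclusion.** The point holds as a cheap improvement. The stated test for the binary safety outcomes cannot bound excess risk, although bounding it is what the study question calls for.

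The size depends on the harm considered. At the protocol's 13.2% rate and 175 per arm, a true 5-point excess is non-significant in about 75% of trials and a 10-point excess in 31% (27% at 193 per arm). It would be wrong to say that non-significance is likely at an excess as large as the trial's own margin: at 13.2% the test detects it about 70% of the time, and at an assumed 5% rate about 90%. Non-significance is likely for excesses of roughly 5 to 7 points at 13.2%, or for rare events. The figures at 20%, 5% and 1% rest on assumed rates.

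Nor do the documents support carrying the 10-point margin over as a requirement. No rate is given for 6 months. For rare events the margin would be nearly empty: at an assumed 1% rate with a true 2-point excess, a Newcombe upper limit falls below 10 points in 98.5% of trials. The primary non-inferiority analysis is not affected.

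**What to change.** In Statistical methods, separate the binary safety outcomes (grade 2 or higher complications at 6 months; bleeding or thrombotic complications at 1 and 6 months) from the general chi-square statement, and specify:

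1. The main result for each is the risk difference, S1 minus S2, with a two-sided 95% confidence interval suited to low counts (Newcombe or Miettinen-Nurminen), in the same populations as the primary analysis. The upper limit is interpreted.
2. Any P value is supportive, from an exact test where counts are sparse.
3. A non-significant P will not be read as evidence of no added risk.

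Comparing the 6-month upper limit with 10 points is optional and descriptive. No margin is proposed for bleeding or thrombosis.

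The cost is analysis-plan wording and a few lines of code, with no extra patients or data. The downside is that the intervals will be wide, so the report will have to say plainly how much excess risk remains possible.

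### The Statistical methods section names an equivalence procedure (TOST), with 0.05 as the only level nearby, for a non-inferiority question that the rest of the protocol defines and sizes by a one-directional two-sided 95% CI rule

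*Protocol article*

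**What the plan says.** Everything below is in the protocol article.

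- **Study design** frames the question in one direction: the trial is to "assess whether maintenance of OAC treatment increases the risk of adverse events (AEs) in patients undergoing PVP".
- **Abstract, Methods** defines success as "not worse than a 10% (non-inferiority margin) inferior change in the proportion of patients with good outcomes", and goes on to specify two-tailed 95% confidence intervals and 80% power.
- **Sample size estimation** repeats this: "Using two-tailed 95% confidence intervals, non-inferiority would be identified with 80% power up to a non-inferiority margin of 10" percent, with about 350 participants and a complication risk of 13.2% assumed under both strategies. One margin is given, and no lower margin appears anywhere.
- **Statistical methods** first states, for the primary endpoint, that "the judgement criterion analysis will be performed using the non-inferiority confidence intervals approach". Its last paragraph then says "To evaluate non-inferiority, the hypothesis testing strategy will follow the two one-sided tests (TOST) procedure". The next sentence reads "To assess superiority, the hypothesis testing strategy will be two-tailed", and the one after it says that a P "value of 0.05 will be considered statistically significant". No separate level is given for one-sided tests.

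**The concern.** TOST is a procedure for equivalence. It must reject two hypotheses: that maintaining treatment (S1) is worse than stopping (S2) by the margin or more, and that it is better by the margin or more. A non-inferiority question needs only the first. TOST also has a usual pairing of level and interval: 0.05 per test corresponds to a 90% interval, whereas a two-sided 95% interval corresponds to 0.025 per test.

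The text can therefore be read as giving two rules for the primary conclusion, which may differ in direction and in error rate. The same data could be declared non-inferior under one and not under the other. The primary endpoint is a safety outcome in anticoagulated surgical patients, so the chance of wrongly declaring non-inferiority should not depend on which sentence the analyst follows.

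**Working it through.** **Inputs.** From Sample size estimation: risk p = 0.132 in both arms, margin m = 0.10, total about 350. The 1:1 allocation in the Abstract gives 175 per arm. Differences are S1 minus S2. TOST needs a second margin; -10 points is my assumption, because the document gives none. Limits use the unpooled (Wald) standard error. The exact figures sum binomial probabilities over all pairs of event counts at 175 per arm, using the same limits.

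**1. Reproduce the plan's figure (one-directional, two-sided 95% CI).**

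n per arm = 2p(1-p)(1.960 + 0.842)² / m² = 0.2292 × 7.85 / 0.01, which rounds up to 180, or 360 in total. This is 2.9% above 350.

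At 175 per arm, SE = √(2 × 0.132 × 0.868 / 175) = 0.0362 and m/SE = 2.763. Power = Φ(2.763 - 1.960) = 78.9% (exact 79.4%). The stated 80% at about 350 therefore belongs to this rule.

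**2. Other rules at the same inputs.**

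| Rule | Power at 350 | Exact | Total N for 80% |
|---|---|---|---|
| One-directional, one-sided 0.025 (95% CI) | 78.9% | 79.4% | 360 |
| One-directional, one-sided 0.05 (90% CI) | Φ(2.763 - 1.645) = 86.8% | 87.0% | 284 |
| TOST ±10 points, 0.05 per side | 2Φ(2.763 - 1.645) - 1 = 73.7% | 74.0% | 394 |
| TOST ±10 points, 0.025 per side | 2Φ(2.763 - 1.960) - 1 = 57.8% | 58.8% | 482 |

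The TOST sizes use 2p(1-p)(z + 1.282)² / m² per arm, with z = 1.645 or 1.960. Only the first row reproduces about 350.

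**3. False non-inferiority at a true +10 points** (13.2% against 23.2%, exact): 2.65% under the 95% CI rule and 5.19% with a single one-sided test at 0.05. Adding the assumed lower bound barely changes the latter (5.14%).

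**4. Data sets on which the rules disagree** (S2 = 23/175, 13.1%).

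| S1 events | Difference, points | 95% CI | 90% CI |
|---|---|---|---|
| 28/175 | +2.86 | -4.53 to 10.24 | -3.34 to 9.06 |
| 29/175 | +3.43 | -4.01 to 10.87 | -2.82 to 9.68 |
| 12/175 | -6.29 | -12.54 to -0.03 | -11.53 to -1.04 |

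For 29/175, SE = √[(0.1657 × 0.8343 + 0.1314 × 0.8686) / 175] = 0.0380, and the upper limits are 3.43 + 1.960 × 3.80 = 10.87 and 3.43 + 1.645 × 3.80 = 9.68.

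With 28 or 29 events, S1 fails the 95% CI rule and passes at 0.05. With 12 events, S1 passes the one-directional rule with ease, yet a full TOST with the assumed -10 bound fails at either level because S1 looks too much better.

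**The case against.** The best defence is that the intended rule can be recovered. Two sections give the one-directional margin with a two-sided 95% interval, the Statistical methods section assigns the primary endpoint to a non-inferiority interval, and the sample size agrees with all three. TOST may be loose wording for a single one-sided test against the margin. The 0.05 sentence comes straight after the superiority sentence and may be only the general two-sided threshold.

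Much of this stands, and it limits what can be claimed. A reader might infer any of the following:

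- *The plan fixes 0.05 for each one-sided test and so doubles the error.* The document does not say so. The rise to 5.2% depends on that reading.
- *S1 will be penalised for doing better, or the trial has only 59% or 74% power.* Both need a lower margin of -10 points that the document never states. With one margin, a full TOST cannot be run as written.
- *The sample size is wrong.* It is not; it fits the interval rule. TOST at 0.05 per side would even reach 79.1% at 386 patients, though only if nobody withdrew, and the added patients are there to cover withdrawals.

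The defence does not remove the conflict. The TOST sentence is expressly about non-inferiority, so it cannot be assigned to secondary outcomes. If TOST means a single one-sided test, 0.05 is still not reconciled with the 0.025 implied by a 95% interval: under the design assumptions 87.0% - 79.4% = 7.6% of trials would change verdict. If the 0.05 sentence is set aside and TOST is run at 0.025, the equivalence bound remains. Nor is this detail left to an analysis plan: the article names a procedure that disagrees with its own definition of success.

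**Conclusion.** The TOST sentence is wrong as written. It names an equivalence procedure for a one-directional question and stands beside an unreconciled 0.05, while the protocol's definition of success and its sample size rest on a two-sided 95% interval against a single 10-point margin. It is the lone outlier, and about 350 patients remains adequate for the interval rule.

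The size of the problem depends on the reading. With 0.05 per one-sided test, false non-inferiority at a true +10 points goes from about 2.6% to 5.2%, and borderline results such as 28 or 29 against 23 events in 175 change verdict. With a full TOST and the assumed -10-point bound, the stated 80% does not apply (about 74% or 59%), and a favourable result such as 12 against 23 events can fail. All figures assume 175 evaluable patients per arm and Wald limits; the power figures also assume 13.2% in both arms.

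**What to change.** Delete the TOST sentence and state one primary decision rule: S1 is non-inferior if the upper limit of the two-sided 95% confidence interval for the risk difference (S1 minus S2, patients with at least one Clavien-Dindo grade 2 or higher complication by day 30) is below 10 percentage points, equivalent to a one-sided alpha of 0.025. Say that the 0.05 level applies to two-sided superiority and secondary tests only. Fixing when superiority is tested relative to non-inferiority is optional and not needed to resolve this point.

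The cost is wording in the protocol, and in the analysis plan if it repeats the sentence. Sample size, data collection and patients are unaffected. The change should be made before outcome data are seen by arm.
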